**Comparative evaluation of effectiveness of standard of care alone and in combination with homoeopathic treatment in COVID-19 related Rhino-orbito-cerebral Mucormycosis (ROCM): A single blind, Randomized Controlled trial**

| **Title** | Comparative evaluation of effectiveness of standard of care alone and in combination with homoeopathic treatment in COVID-19 related Rhino-orbito-cerebral Mucormycosis (ROCM): A single blind, Randomized Controlled trial |
| --- | --- |
| Short Title | *Role of adjuvant homoeopathy in COVID related ROCM* |
| Methodology/Design | Randomised control, single blind, parallel group trial |
| Study Duration | 3 months |
| Study Centre(s) | **St. George’s and JJ Hospital, Mumbai** /Any other |
| Introduction | Recently, several cases of mucormycosis in people with COVID19 have been increasingly reported world-wide, in particular from India. The primary reason that appears to be facilitating Mucorales spores to germinate in people with COVID-19 is an ideal environment of low oxygen (hypoxia), high glucose (diabetes, new-onset hyperglycemia, steroid-induced hyperglycemia), acidic medium (metabolic acidosis, diabetic ketoacidosis [DKA]), high iron levels (increased ferritins) and decreased phagocytic activity of white blood cells (WBC) due to immunosuppression (SARS-CoV-2 mediated, steroid-mediated or background comorbidities) coupled with several other shared risk factors including prolonged hospitalization with or without mechanical ventilators.^[[1]](#endnote-1)^ Use of Homoeopathy as adjuvant to Standard Treatment has helped faster and better recovery in previous fungal infection. This knowledge may be put to use, and further validated in the treatment COVID related rhino-orbito-cerebral mucormycosis. The details are given in introduction section. |
| **Objectives** | **Primary Objective**   - To evaluate the role of adjuvant homoeopathy in treatment of covid-related ROCM patients through standard parameters in respective conditions   **Secondary Objective**   - To enhance the survival of the patients hospitalized due to covid-related mucormycosis |
| **Patients and Methods** | Patients hospitalised for treatment of covid-related ROCM will be provided Homoeopathy as adjuvant treatment with standard treatment care, after informed consent in one arm, and standard treatment care alone in the other. |
| **Number of Subjects (Sample Size)** | 72 (36 each arm); explained in Section 3.7) |
| **Inclusion Criteria** | - Stage 1 and 2 (Staging document annexed) of ROCM - Age > 18 years - All genders - Fungal smear analysis through KOH staining/ microscopy of affected area showing presence of mucormycetes (to save precious time), followed by following exploratory imaging techniques:   - CEMRI (for ruling out Stages 3 and 4)   - CT-guided endoscopy-cum-biopsy (for detailed histopathology study) |
| **Exclusion Criteria** | - ROCM cases in stages 3 and 4(Staging document annexed) presenting with bony erosion, cerebral vascular invasion, invasion into the cranium, orbital apex or cribriform plate of the ethmoid bone, cavernous sinus (II-VI cranial nerve palsies) will be excluded. - Diagnosed cases of Pulmonary ,Cutaneous, Gastrointestinal ,Advanced, disseminated mucormycosis will be excluded. - Pregnant and lactating women. - In the opinion of the clinical team, progression to death is imminent and inevitable within the next 24 hours, irrespective of the provision of treatments. |
| **Follow-up period** | - Patient will be assessed clinically twice a day; MRI/endoscopy-cum-biopsy will be assessed on day 1, 14 and 28. |
| **Outcomes** | **Primary Outcome**   1. Change in condition as seen in standard imaging or other diagnostic techniques:  - MRI contrast in ROCM cases   **Secondary Outcomes**   1. To assess difference in the survival of the patients in both the groups during hospitalization. |
| **Endpoint** | - Recovery as per the outcome parameters, followed by discharge from hospital - Advanced, disseminated mucormycosis - Death of the patient |
| **Study Product, Dose, Route** | - Individualized homoeopathic medicine in appropriate dose, orally, four times daily; or more frequently in severe cases. |
| Placebo | Placebo group patients will receive identical placebo (globules moistened with dispensing alcohol) as an add on to standard protocol treatment. Dose repetition will be a in similar pattern to medicine group. |
| Duration of administration | Maximum 28 days (depending on the patient’s admission duration) |
| Statistical Methodology | All primary efficacy analyses will be conducted in the Intention-to-treat (ITT) population; thus, all randomized patients should be included in the primary analysis. |
| Funding Agency | Central Council for Research in Homoeopathy, Ministry of AYUSH, Govt. of India |
| Budget | Rs. 75 lakhs approx. |

# Introduction

## Background

The pandemic coronavirus disease 2019 (COVID-19) continues to be a significant problem worldwide. In the absence of an effective vaccine or antiviral therapy, supportive care plays a vital role in the management of COVID-19. Glucocorticoids and probably remdesivir are the only drugs proven to be beneficial in COVID-19. Unfortunately, the widespread use of glucocorticoids can lead to secondary bacterial or fungal infections. The immune dysregulation caused by the virus and the use of concurrent immunomodulatory drugs such as tocilizumab also increased the risk of infections in COVID-19 patients.^[[2]](#endnote-2),^^[[3]](#endnote-3),^^[[4]](#endnote-4)^

Mucormycosis is caused by a group of molds called mucormycetes, which are found in the environment and release spores that are easily aerosolized and dispersed^[[5]](#endnote-5)^ . The most common genera that cause infections in humans are Rhizopus and Mucor species, but others include Apophysomyces, Rhizomucor, Cunninghamella, Lichtheimia, Cokeromyces, and Saksenaea^[[6]](#endnote-6)^. The Rhizopus Oryzae is most common type and responsible for nearly 60% of mucormycosis cases in humans and also accounts Journal Pre-proof for 90% of the Rhino-orbital-cerebral (ROCM) form^[[7]](#endnote-7)^ . Mode of contamination occurs through the inhalation of fungal spores.

Both Aspergillosis and Candida have been reported as the main fungal pathogens for co-infection in people with COVID-19^[[8]](#endnote-8)^ . Recently, several cases of mucormycosis in people with COVID19 have been increasingly reported world-wide, in particular from India. The primary reason that appears to be facilitating Mucorales spores to germinate in people with COVID-19 is an ideal environment of low oxygen (hypoxia), high glucose (diabetes, new-onset hyperglycemia, steroid-induced hyperglycemia), acidic medium (metabolic acidosis, diabetic ketoacidosis [DKA]), high iron levels (increased ferritins) and decreased phagocytic activity of white blood cells (WBC) due to immunosuppression (SARS-CoV-2 mediated, steroid-mediated or background comorbidities) coupled with several other shared risk factors including prolonged hospitalization with or without mechanical ventilators.^[[9]](#endnote-9)^ One of the systematic review showed that mucormycosis was predominantly seen in males (78.9%), both in people who were active (59.4%) or recovered (40.6%) from COVID-19. Hyperglycemia at presentation (due to pre-existing DM or new-onset hyperglycemia or new-onset diabetes or diabetic ketoacidosis [DKA]) was the single most important risk factor observed in majority of cases (83.3%) of mucormycosis in people with COVID-19, followed by cancer (3.0%).Studies suggested that covid-19 is associated with destruction of β-cell of the pancreas^[[10]](#endnote-10)^, ^[[11]](#endnote-11)^. History of corticosteroid intake for the treatment of COVID-19 was present in 76.3% of cases, followed by remdesivir (20.6%) and tocilizumab (4.1%). Commonest organ involved with mucormycosis was nose and sinus (88.9%), followed by rhino-orbital (56.7%) and ROCM type (22.2%). ^[[12]](#endnote-12)^ Uncontrolled hyperglycemia and precipitation of Diabetic Ketoacidosis is often observed due to corticosteroid intake. Low pH due to acidosis is a fertile media for mucor spores to germinate.

Moreover, steroid use reduces the phagocytic activity of WBC (both first line and second line defense mechanism), causes impairment of bronchoalveolar macrophages migration, ingestion, and phagolysosome fusion, making a diabetic patient exceptionally vulnerable to mucormycosis. COVID-19 often causes endothelialitis, endothelial damage, thrombosis, lymphopenia, and reduction in CD4+ and CD8+ level and thus predisposes to secondary or opportunistic fungal infection.^[[13]](#endnote-13)^

Mucormycosis can affect nearly any part of the body, with rhinocerebral and pulmonary infections caused by inhalation of spores, and cutaneous infections caused by spores entering the skin. Gastrointestinal mucormycosis can occur when contaminated foods or products are introduced to the GI tract. Mucormycetes can infiltrate blood vessels and spread to the brain and other organs through the bloodstream, resulting in disseminated infections.^[[14]](#endnote-14)^

Mucormycosis is characterised by the presence of hyphal invasion of sinus tissue and a time course of less than four weeks ^[[15]](#endnote-15)^, ^[[16]](#endnote-16)^ Clinically, rhinocerebral mucormycosis can present with atypical signs and symptoms, the initial symptoms of rhinocerebral mucormycosis are consistent with either sinusitis or periorbital cellulitis^[[17]](#endnote-17)^, ^[[18]](#endnote-18)^ and include eye or facial pain and facial numbness, followed by the onset of conjunctival suffusion, blurry vision, and soft tissue swelling^[[19]](#endnote-19)^ ^[[20]](#endnote-20)^ ^[[21]](#endnote-21)^. Fever is variable and may be absent in up to half of cases^[[22]](#endnote-22)^ . If untreated, infection usually spreads from the ethmoid sinus to the orbit, resulting in loss of extraocular muscle function and proptosis. Diplopia and marked chemosis may also be seen. The infection may rapidly extend into the neighboring tissues. On set of signs and symptoms in the contralateral eye, with resulting bilateral proptosis, chemosis, vision loss, and ophthalmoplegia, is an ominous sign that suggests the development of cavernous sinus thrombosis. Upon visual inspection, infected tissue may appear normal during the earliest stages of spread of the fungus. Infected tissue then progresses through an erythematous phase, with or without edema, before onset of a violaceous appearance, and finally the development of a black, necrotic eschar as the blood vessels become thrombosed and tissue infarction occurs^[[23]](#endnote-23)^ Infection can sometimes extend from the sinuses into the mouth causes loosening of teeth and often produce painful, necrotic ulcerations of the hard palate^[[24]](#endnote-24)^. Cranial nerve findings represent extensive infection and signal a grave prognosis. Progressive vision loss and ultimately blindness may result either from involvement of the optic nerve or from arteriolar invasion resulting in infarction^[[25]](#endnote-25)^ ^[[26]](#endnote-26)^ ^[[27]](#endnote-27)^ or from cavernous sinus thrombosis. Cranial nerves five and seven may also be affected, resulting in ipsilateral loss of facial sensation and ptosis and pupillary dilation ^[[28]](#endnote-28)^, ^[[29]](#endnote-29)^ Infection can also spread posteriorly from either the orbit or sinuses to the central nervous system. A bloody nasal discharge may be the first sign that infection has invaded through the terbinates and into the brain. When there is extensive central nervous system involvement, the angioinvasive nature of the fungus may result in cavernous sinus thrombosis and internal carotid artery encasement and thrombosis with extensive resulting cerebral infarctions^[[30]](#endnote-30)^ ^[[31]](#endnote-31)^ ^[[32]](#endnote-32)^. Occasionally cerebral vascular invasion may lead to hematogenous dissemination of the infection ^[[33]](#endnote-33)^ with or without development of mycotic aneurysms^[[34]](#endnote-34)^.

Pulmonary mucormycosis may develop as a result of inhalation or by hematogenous or lymphatic spread. Symptoms of pulmonary mucormycosis includes refractory fever on broad-spectrum antibiotics, non-productive cough, progressive dyspnea, pleuritic chest pain^[[35]](#endnote-35)^. High-resolution chest CT scan is the
best method of determining the extent of pulmonary mucormycosis and may demonstrate evidence of infection before it is seen on the chest x-ray^[[36]](#endnote-36)^.

Patients with skin barrier disruptions (burns, trauma, catheter insertion, injections) or persistent skin maceration are at increased risk for cutaneous mucormycosis ^[[37]](#endnote-37)^. The fungus can invade into adjacent fat, muscle, fascia, and even bone, while secondary vascular invasion and hematogenous spread are less common ^[[38]](#endnote-38)^ ^[[39]](#endnote-39)^ . However, cutaneous mucormycosis with hematogenous dissemination has high fatality rates ^[[40]](#endnote-40)^. **Gastrointestinal mucormycosis is** mainly occurs in patients who are extremely malnourished (especially infants or children) and is thought to arise from ingestion of the fungi. In particular, gastrointestinal mucormycosis has been seen in premature neonates, often in association with widespread disseminated disease.^[[41]](#endnote-41)^ ^[[42]](#endnote-42)^ ^[[43]](#endnote-43)^ ^[[44]](#endnote-44)^. The stomach, colon, and ileum are the most commonly involved sites. The stomach, colon, and ileum are the most commonly involved sites. The diagnosis may be made by biopsy of the suspected area during surgery or endoscopy.^[[45]](#endnote-45)^ .

Diagnosis of mucormycosis remains challenging. Clinical approach to diagnosis has a low sensitivity and specificity, it helps however in raising suspicion and prompting the initiation of laboratory testing. Histopathology, direct examination and culture remain essential tools, although the molecular methods are improving. Histological features include mycotic infiltration of blood vessels, vasculitis with thrombosis, tissue infarction, haemorrhage and acute neutrophilic infiltrate.^[[46]](#endnote-46)^^[[47]](#endnote-47)^, however, of a necrotic eschar does not preclude the diagnosis ^[[48]](#endnote-48)^ ^[[49]](#endnote-49)^. A definitive diagnosis is based on the demonstration of fungal hyphae typical for mucormycetes in biopsies of affected tissues, or bronchoalveolar lavage (BAL) in patients with pulmonary mucormycosis. Histopathology is a very important diagnostic tool since it distinguishes the presence of the fungus as a pathogen in the specimen from a culture contaminant and is indispensable to define whether there is blood vessel invasion.^[[50]](#endnote-50)^ Radiologically, multiple (≥10) nodules and pleural effusion are reportedly associated with pulmonary mucormycosis. Another finding on computerized tomography (CT) scan, which seems to indicate the presence of mucormycosis, is the reverse halo sign. Microscopy (direct and on histopathology) and culture are the cornerstones of diagnosis. Molecular assays can be used either for detection or identification of mucormycetes, and they can be recommended as valuable add-on tools that complement conventional diagnostic procedures.^[[51]](#endnote-51)^ MRI is a valuable modality that can be used to diagnose mucormycosis infections involving sino-nasal region, orbits, and possible intracranial extension. The multiplanar capabilities of MRI with its superior soft tissue depiction are helpful in delineating the anatomical extent of disease as well as its complications^[[52]](#endnote-52)^.

Another emerging imaging technique, which may eventually aid in the diagnosis and management of mucormycosis is the positron emission tomography-computed tomography (PET/CT) with [18F]- fluorodeoxyglucose (FDG).^[[53]](#endnote-53)^ When feasible, endobronchial ultrasound-guided fine needle aspiration is also a useful diagnostic tool.^[[54]](#endnote-54)^

The management of fungal infection includes administration of antifungal therapeutics with and without surgical interventions.^[[55]](#endnote-55)^ Surgery is necessary due to the massive amount of tissue necrosis occurring during mucormycosis, which may not be prevented by killing the organism.^[[56]](#endnote-56)^ In rhinocerebral mucormycosis, early surgical excision of the infected sinuses and appropriate debridement of the retroorbital space can often prevent the infection from extending into the eye^[[57]](#endnote-57)^, There is growing scientific reports on immune response of antifungal medication but still a large number of studies are not clinical based. Here, in case of fungal infection host response involves both cellular and humoral immunity. However, humoral immunity plays a larger role in offering protection against fungal infection. It has been also reported that cellular immunity associated with Th1-type offer a protectiveresponses against fungal infection via secreting IFN-y. On the contrary, the response of Th2 via IL4 and IL10 triggers and facilitate fungal infection and pathological outcomes. Further, mononuclear immune cells start infiltration at the site of infection and offering a delayed immune activity favoring fungal infections.^[[58]](#endnote-58)^ The poor immune surveillance and cellular immune activity was reported during chronic inflammatory diseases including diabetes and cancer.^[[59]](#endnote-59)^

The homoeopathy system includes a holistic approach, the medicines are selected on the basis of presenting signs and symptoms of each patient^[[60]](#endnote-60)^.Fungal infections are amenable to homoeopathic treatment. Various research studies undertaken on various fungi in-vitro model showed that homoeopathy medicine could prevent the growth of the fungus. prajapatiet al showed that homoeopathic medicines Syzygium jambolanum, Ficus religiosa, Ocimum sanctum, Allium cepa, Thuja occidentalis, Holarrhenaantidysenterica and Eucalyptus globulus showed signifi cant inhibitory activity against the growth of Candida. albicans^[[61]](#endnote-61)^, whereas gupta et al. study shown that homoeopathic medicines Mezereum in 200 and 30 potency showed maximum inhibition of growth of Candida albicans. ^[[62]](#endnote-62)^ ^[[63]](#endnote-63)^. Another invitro study demonstrated that homoeopathic drugs, namely Zingiber officinale, Holarrhenantidysenterica, Terminalia chebula, Allium cepa, Caesalpinia bonducella, Eucalyptus globulus, Ruta graveolens and Thuja occidentalis have significant antifungal activity against human pathogenic fungi Aspergillus niger.^[[64]](#endnote-64)^

Symptomatic Homoeopathy management of Suspected and Diagnosed cases of Mucormycosis has been advised in Guidelines by Ministry of AYUSH.^[[65]](#endnote-65)^ These guidelines will play a vital role in identification of the indicated medicines in this proposed study.

**Hypothesis**

Homoeopathic treatment, as an adjuvant to standard of care given to patients suffering from COVID-related mucormycosis, can lead to better recovery of the patients.

# OBJECTIVES:

## Primary Objective

- To evaluate the role of adjuvant homoeopathy in treatment of covid-related ROCM patients through standard parameters in respective conditions

## Secondary Objectives

- To enhance the survival of the patients hospitalized due to covid-related mucormycosis

# Material & Methods

## 3.1 STUDY DESIGN

Study design is single blind, randomized clinical trial.

Of the 2 groups running in parallel, the control arm will receive conventional treatment as per IMP, while the other group will receive homoeopathic intervention along with IMP. Allocation ratio will be 1:1 through randomisation obtained from computerised random number generator.

## 3.2 STUDY SETTING

**The trial will be conducted at** **St. George’s and JJ Hospital, Mumbai with informed consent of the patients admitted in the IPD for treatment of COVID related mucormycosis.**

## 3.3 ELIGIBILITY CRITERIA

### INCLUSION CRITERIA:

- Confirmed cases* of covid-related ROCM .
- Age > 18 years
- All genders
- ***Confirmation of each type of mucormycosis will be based upon** respective inclusion criteria:

| **S.No** | **Type of Mucormycosis** | **Inclusion criteria** |
| --- | --- | --- |
|  | **ROCM** | - Stage 1 and stage 2 (Staging document annexed) of ROCM will only be included). - Fungal smear analysis of the affected site reporting presence of mucormycetes (to save precious time), followed by MRI and/or biopsy - *MRI contrast imaging**   *MRI will show Mucosal thickening with T2 hypointense components at T2W images, Nonenhancement of involved mucosa/soft tissue at Post contrast T1W images, Marrow edema and enhancement of adjacent bones and skull base at Fat- saturated T2W and postcontrast T1W image. ^[[66]](#endnote-66)^ . Hyperintense lesion extending from paranasal sinus along orbital apex into intracranial structures and narrowing or slow flow in the ipsilateral internal carotid artery in the vicinity of mucor invasion seen in T2W^[[67]](#endnote-67)^.   - KOH staining/ microscopy and Biopsy**** of affected area   ****Biopsy will show non-septate/pauci-septate, ribbon-like hyphae (at least 6–16μm wide), Vessel occlusion)^[[68]](#endnote-68)^. |

### EXCLUSION CRITERIA:

- **ROCM:** Cases in stages 3 and 4(Staging document annexed) presenting with bony erosion, cerebral vascular invasion, invasion into the cranium, orbital apex or cribriform plate of the ethmoid bone, cavernous sinus (II-VI cranial nerve palsies) will be excluded.
- **Diagnosed cases of Pulmonary, Cutaneous, Gastrointestinal , Advanced disseminated mucormycosis will be excluded.**
- Pregnant and lactating women
- In the opinion of the clinical team, progression to death is imminent and inevitable within the next 24 hours, irrespective of the provision of treatments.

## 3.4 INTERVENTION

Through Patient Information Sheet, patient will be duly informed about equal chances of getting placebo or homoeopathic medicine, depending on the group s/he’s allotted, and then consent will be taken. Moreover, patients will be getting standard care of conventional medicine in both groups, and, therefore, would not be at risk.

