### Details of intervention:

A detailed history and examination will be gathered from the already available information of the patient in the admission records at hospital. The patients randomised into experimental group will be interrogated by the homoeopathic physician only for the additional information required from Homoeopathy perspective.

As per each case, individualized homoeopathic medicine will be prescribed. Symptomatic Homoeopathy management of Suspected and Diagnosed cases of Mucormycosis has been advised in Guidelines by Ministry of AYUSH.^[[69]](#endnote-69)^ These guidelines will play a vital role in identification of the indicated medicines in this proposed study.

Daily recording of the administered dose will be recorded and also captured in the Case Record Form (CRF) developed by the Homoeopathy team, which will be having content other than, and in addition to the standard form, which will be filled at the hospital. If there is any change in dosage / prescription of medications during the study period, that will be mentioned with reason in the prescription chart. If these medicines are stopped, that too would be recorded with reason.

The patients assigned to the placebo group will be given placebo in the form of similar looking homoeopathic pills of 30 size, dispensed with the 30% V/V dispensing alcohol.

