## 3.6 OUTCOMES

#### Primary:

Change in condition as seen in standard imaging or other diagnostic techniques:

- MRI contrast in ROCM cases

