#### Secondary:

- To assess difference in the survival of the patients in both the groups during hospitalization.

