## LABORATORY INVESTIGATIONS

| **INVESTIGATIONS** | | |
| --- | --- | --- |
| - **Lab parameters** | CBC, ESR, FBS, PPBS, HbA1C, LFT, KFT with electrolytes | D0 and as per IMP |
| - **Imaging technique** | - CEMRI of Brain with orbits and sinuses. | - (Only at inclusion) |
|  | - CEMRI PNS | - D0 (or latest report if it is within 03 days of enrolment day), D14 and D28, or before or after as per IMP/ requirement |
|  | - CT guided endoscopy-cum-biopsy Fungal smear/KOH staining | - As per IMP, if required |

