## Insurance

CCRH will provide compensation and insurance cover in the trial for the said duration of study, according to the terms finalized under clinical trial cover with the identified insurance firm.

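### The protocol infers absence of risk from standard care in both arms and plans no adverse-event collection, so most non-fatal harm cannot be reported by arm

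*Protocol*

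**What the plan says.** On risk, section 3.4 (Intervention) tells the reader that "patients will be getting standard care of conventional medicine in both groups, and, therefore, would not be at risk".

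On the product, the synopsis describes it as "Individualized homoeopathic medicine in appropriate dose, orally, four times daily; or more frequently in severe cases", and the subsection on details of intervention says "As per each case, individualized homoeopathic medicine will be prescribed", with a ministry guideline cited to help choose the medicine. No potency and no upper limit on frequency are stated.

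On outcomes, section 3.6 lists a primary outcome, "Change in condition as seen in standard imaging or other diagnostic techniques" (contrast MRI), and a secondary outcome, "To assess difference in the survival of the patients in both the groups during hospitalization".

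On records, doses, changes of prescription and reasons for change are kept, and "If these medicines are stopped, that too would be recorded with reason". Blood count, liver and kidney tests are timed "D0 and as per IMP". The section on data collection methods also keeps physicians' observations at each visit and all laboratory reports.

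**The concern.** The statement on risk is a conclusion without a supporting premise. Equal standard care in both arms answers the question of whether anyone is deprived of treatment. Whether the added product can do harm is a different question, and nothing in section 3.4 addresses it.

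That would matter little if the trial were set up to check the statement, but the available text has no adverse-event system. A trial that calls itself Phase II, in a life-threatening infection, would then end without an adverse-event table. It could not set benefit against non-fatal harm when the product is added to standard care, and its own assurance to patients could not be tested against its own data. A later analysis plan cannot repair this, because it can only summarise what was collected.

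**Working it through.** The plan gives no safety figure to reproduce, so the check is mainly a reading of each place where an adverse-event provision would sit.

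**Step 1. Where a provision would be expected**

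| Protocol section | What it contains | Adverse-event provision |
| --- | --- | --- |
| 3.5 Withdrawal | spread beyond the eligible stages, ventilator need, unwillingness or non-compliance | none; a suspected reaction is not a ground |
| 3.6 Outcomes | MRI change; in-hospital survival | none |
| Laboratory investigations | blood count, liver and kidney tests fixed only at D0, then by the care protocol; sinus MRI at D0, D14, D28 | no trial safety schedule |
| Data collection methods | case record form, database of physician observations, laboratory reports, homoeopathy records | no adverse-event form named |
| Statistical analysis; Statistical methods | tests for categorical and numerical data, ITT, subgroups, correlations | no safety analysis |
| Ethics and dissemination | approval, insurance, consent, confidentiality, data access | no reporting route for serious events |

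**Step 2. What would still be seen**

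- In-hospital survival is compared by arm, and the synopsis names death and disseminated disease as endpoints.
- Spread beyond the eligible stages and ventilator need appear as withdrawal grounds.
- Other events may appear in twice-daily clinical assessments, physician observations, laboratory reports, and reasons for changing or stopping a medicine. These are unstructured: no event definition, severity, seriousness or relation to the product is asked for.

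**Step 3. How a possible reaction would be handled**

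Under the change-of-prescription subsection, the medicine is changed if laboratory results do not move or if the patient reports feeling unwell after at least three doses. A patient unwell because of the product and a patient unwell because it does nothing follow the same path. The recorded reason need not separate them.

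**Step 4. What capture would give with the planned numbers**

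Input: 36 per arm (synopsis). The event rates below are assumptions; the protocol gives none.

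- Upper one-sided 95% limit after zero events in n patients: 1 − 0.05^(1/n). For n = 36 this is 1 − 0.05^(1/36) = 0.080, about 8%.
- Chance of seeing at least one event in an arm: 1 − (1 − r)^36. This is 30% for a true rate r of 1%, 52% for 2%, 84% for 5% and 98% for 10%.
- Between-arm difference detectable with 80% power (two-sided 5%, 36 per arm): about 5% versus 30%, 10% versus 38%, or 20% versus 51%.

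The sample-size section gives (1.96 + 0.84)² × 0.09 / 0.10² = 70.56 and asks for 71 per group, yet enrols 72 in all. That inconsistency is a separate matter. With 71 per arm the zero-event limit would be 1 − 0.05^(1/71) = 0.041, about 4%.

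**The case against.** The strongest reply is that the sentence on risk is read too literally. It follows the explanation that patients have equal chances of placebo or medicine, so its natural sense is that placebo allocation deprives no one of conventional treatment. That reading is fair, and the narrower statement would be sound. The words used go further, and they sit in the section describing what patients are told before consent.

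A second reply is that safety tables are commonly left to an analysis plan and that the case record form is not shown. The layout of a table can indeed be left to an analysis plan. Whether events are defined and collected belongs in the protocol. The form may contain an adverse-event page, and a small part of the public text was removed, so the absence is judged on the available text.

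Several stronger inferences are tempting and are not supported:

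- *The trial cannot detect harm.* Survival is compared by arm, and progression, ventilator need and repeat MRI are observed.
- *An event that changes no medicine leaves no record.* Physician observations and laboratory reports are kept for every patient. What is missing is a defined and systematic record.
- *Potency and frequency are unrestricted.* A default of four times daily is given and a guideline is cited. The text supports only that potency is not stated and that no maximum frequency is set.
- *Every active-arm patient takes at least 112 doses.* The product 4 × 28 = 112 uses the synopsis's maximum of 28 days. Patients discharged, withdrawn or dying early may take fewer.
- *Insurance contradicts the no-risk statement.* The protocol says "CCRH will provide compensation and insurance cover in the trial", but such cover is no admission of risk from the product.
- *Adverse events are omitted because patients are thought not to be at risk.* The protocol draws no such link.

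**Conclusion.** The point holds in a limited form. The no-risk inference does not follow from standard care in both arms. On the available text, adverse and serious adverse events are neither defined, nor systematically collected, nor reported by arm. Beyond in-hospital survival, progression, ventilator need and unstructured notes or laboratory reports, non-fatal harm cannot be reported by arm.

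This affects all 72 planned patients. Capture would not make the trial a sensitive safety comparison: with 36 per arm only large differences are detectable. It would allow a table by arm and a stated limit, about 8% after zero events of a given type, where the present plan allows neither. The 8% assumes 36 evaluable patients per arm and complete capture.

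The efficacy analysis is unaffected. The change is worth making because it is inexpensive and cannot be made after the data are in.

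**What to change.** 1. In section 3.4, delete the conclusion that patients are not at risk, or limit it to saying that no patient in either arm is deprived of standard care.
2. Define adverse and serious adverse events in the protocol and record them on the case record form, identically in both arms, from first dose to Day 28. Use the twice-daily assessments and the Day 14 and Day 28 contacts already planned, including the telephone contacts after discharge. A separate section gives 30 days of administration; the sponsor should reconcile the two durations so that the collection window covers the whole treatment period.
3. Add safety to section 3.6 as an outcome reported by arm, together with the laboratory reports already retained.
4. Have the recorded reason for a change or stop of study medicine distinguish a suspected reaction from lack of effect, and state how a suspected reaction is handled. The content of that clinical rule, and any dose or potency, are for the sponsor; none is proposed here.

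The cost is roughly one form page, one summary table and a small amount of extra data entry. No new visit or test is needed.
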